### Study procedures and data collection

Data at baseline, one month and 3 months after the intervention will be collected.

### Statistical and cost-effectiveness analyses

Demographic and baseline analyses will be conducted to ensure random allocation procedure has been effective in producing comparable study arms. Chi-square, *t*-test, repeated measure ANOVA and logistic regression analyses will be the primary modes of analyzing the results. As the primary outcomes, we will assess the effects of the study arms on the proportion of prescriptions containing each of the target prescribed medicines. We will also assess the effects of the interventions on the mean cost per prescription, and the mean number of items prescribed per prescription. Appropriate interaction analyses will be conducted to assess the interactions between the selected variables and the interventions. A fixed-effect two-level analysis approach will be followed in which prescriptions will be used as the first level and the physicians as the second level of data.

Cost data will be assessed using the actual costs incurred in the study, from a health care provider view point. Incremental cost-effectiveness ratios will be calculated and sensitivity analyses will be also conducted to assess the effects of changes in important variables in the cost-effectiveness of the interventions.

Intention-to-treat analyses will be carried out with physicians as the primary analysis approach. We will also conduct a per protocol analysis as a sensitivity analysis.

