**Method/design:**

A four-arm randomized trial with economic evaluation will be conducted in Tehran. Three interventions (routine feedback, revised feedback, and printed educational material) and a no intervention control arm will be compared. Physicians working in outpatient practices are randomly allocated to one of the four arms using stratified randomized sampling. The interventions are developed based on a review of literature, physician interviews, current experiences in Iran and with theoretical insights from the Theory of Planned Behavior. Effects of the interventions on improving antibiotics and corticosteroids prescribing will be assessed in regression analyses. Cost data will be assessed from a health care provider’s perspective and incremental cost-effectiveness ratios will be calculated.

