### Outcome measures

The main outcome measures for assessing the effectiveness of the interventions, the percentage of change in the proportion of dexamethasone injectable form, oral form of cefixime and amoxicillin which prescribed by general physicians, pediatricians and infectious disease specialists will be considered.

Costs are assessed from a health care provider perspective. We include all identifiable costs related to the implementation of the interventions. Our analysis therefore focuses on the incremental costs of developing and implementing audit and feedback and printed educational material interventions. Recurring and non-recurring costs are considered. Nonrecurring costs include revising the computer software and designing the new format of the feedback, and the pamphlet. Recurring costs include printing materials, travel costs, postage costs and other administrative tasks.

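### Four methods are all called primary, none is named as decisive for the primary outcomes, and they are not reconciled with the two-level model stated in the same section

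*Protocol article*

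**What the plan says.** All places are in the protocol article.

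- **Statistical and cost-effectiveness analyses, methods:** "Chi-square, *t*-test, repeated measure ANOVA and logistic regression analyses will be the primary modes of analyzing the results". No order or decision rule is given.
- **Same section, next sentence, primary outcomes:** "we will assess the effects of the study arms on the proportion of prescriptions containing each of the target prescribed medicines". Two continuous outcomes follow as additional assessments: "the mean cost per prescription, and the mean number of items prescribed per prescription".
- **Same section, model:** "A fixed-effect two-level analysis approach will be followed in which prescriptions will be used as the first level", with physicians as the second level.
- **Same section, population:** "Intention-to-treat analyses will be carried out with physicians as the primary analysis approach". Here the word primary describes the analysis set, not a test.
- **Outcome measures:** the main outcome is worded as a change, "the percentage of change in the proportion of dexamethasone injectable form, oral form of cefixime and amoxicillin".
- **Abstract, Method/design:** "Effects of the interventions on improving antibiotics and corticosteroids prescribing will be assessed in regression analyses".
- **Study procedures and data collection:** measurements at baseline, one month and three months.

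The article gives no significance level, sidedness or false-positive rate.

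**The concern.** The sentence on methods is a positive choice, not a gap: it gives four procedures equal primary standing. Three things follow.

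First, the four do not sit easily with the model stated a few lines later. A plain chi-square test or t-test is not a two-level analysis of prescriptions within physicians, and neither is a regression, which is what the abstract announces.

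Second, the methods can address different questions about the same medicine. A t-test can compare physician-level shares at follow-up, or their change. The arm-by-time term of a repeated-measures ANOVA compares trajectories. Run across all four arms, it is an omnibus test and does not by itself answer the arm-versus-arm questions listed as objectives at the end of the Background.

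Third, if two of these give different answers on a borderline effect, either could truthfully be described as one of the pre-specified primary analyses. The Discussion says that cost-effective interventions should be applied widely across the country, so which result decides the trial should be fixed in advance.

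**Working it through.** **Plan's own figure.** There is none to reproduce, because no error rate is stated. Everything below is conditional on assumptions.

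**Inputs from the article.** 203 physicians per arm; about 14% of prescriptions with injectable dexamethasone; at least 100 prescriptions per physician per month; three measurement times.

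**Assumptions.** Two-sided 5% per test. Any significant test among those called primary may be reported as the result. One medicine, one two-arm contrast, three-month result; the ANOVA also uses the earlier times. Intra-physician correlation 0.02 to 0.10; correlation of physician effects over time 0.5 to 0.9. The article gives none of these.

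**Step 1: tests on the same summary.** In null simulations (3,000 trials per setting, 100 or 300 prescriptions per physician), the t-test and the cluster-robust chi-square and logistic tests were all applied to the final proportion. The chance that at least one was significant was 4.5-5.6%, so there is almost no inflation.

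**Step 2: add the arm-by-time ANOVA.** With two arms and two occasions, the arm-by-time test is the t-test on the change score. Let r be the correlation of a physician's baseline and follow-up proportions, with equal variances. The follow-up test and the change test then correlate at √((1 − r)/2).

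| r | Correlation of the two tests | P(at least one significant) |
|---|---|---|
| 0.02 | √(0.98/2) = 0.7 | 8.4% |
| 0.28 | √(0.72/2) = 0.6 | 8.8% |
| 0.50 | √(0.50/2) = 0.5 | 9.1% |
| 0.82 | √(0.18/2) = 0.3 | 9.5% |

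The last column comes from 400,000 draws of correlated normal statistics. The simulation of Step 1 with the ANOVA added, on two or three occasions, gave 8.5-10.2%. Both say about 9%.

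**Step 3: add a baseline-adjusted regression.** A separate null simulation (4,000 trials per setting, 100 prescriptions per physician per time) combined the follow-up t-test, the arm-by-time ANOVA and a physician-level baseline-adjusted regression standing in for logistic regression. With between-month correlations of 0.5, 0.7, 0.8 and 0.9, at least one test was significant in 10.4%, 10.7%, 10.7% and 11.5% of trials. The simulation error is √(0.115 × 0.885/4000) = 0.5 percentage points. Steps 2 and 3 together give roughly 9-11%.

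**Step 4: outer bounds for four tests.** Independent tests would give 1 − 0.95⁴ = 18.5%. Equal correlations of 0.5, 0.7, 0.9 and 0.99 give 15.7%, 13.1%, 9.4% and 6.3%; identical tests give 5%. Independence is only a ceiling, since tests on the same data are correlated.

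**Step 5: after the fix.** One pre-named test that allows for physicians stays near 5%: the single valid tests simulated at 4.4-5.9%.

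**The case against.** The strongest reply is that the sentence describes a toolkit. It speaks of the results in general, follows a sentence on baseline comparisons, and precedes outcomes of two kinds. Chi-square and logistic regression suit the binary outcomes; the t-test and repeated-measures ANOVA suit mean cost and mean items. On that reading no outcome has four primary tests. Moreover, logistic regression, the two-level sentence and the abstract's reference to regression together point to a two-level logistic model, and assigning tests to outcomes is ordinarily left to an analysis plan.

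Much of this stands. A reader might infer that all four tests will be run on the same outcome; the article does not say so. A reader might also infer that each comparison carries a 10-15% false-positive risk. That is not supported: no rule says that any one significant test counts as success, and no significance level is given. Simulated values of 13.5-15% arise only when a chi-square test on whether each physician's share fell is added, and the article nowhere dichotomises physicians in that way. Nor should one argue from how often the t-test and the adjusted regression disagree when at least one is significant (56-85% in simulation). With each test at 5%, a conditional share d corresponds to d × 0.10/(2 − d) of all null trials: 0.56 × 0.10/1.44 = 3.9% and 0.85 × 0.10/1.15 = 7.4%. Nor do all four necessarily test different hypotheses: an unadjusted logistic regression and a chi-square test address the same null.

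What the reply does not remove is the wording itself. The primary outcomes are named directly after the list, and the change wording under Outcome measures lets one medicine be analysed as a binary outcome, a level, a change or a trajectory. An analysis plan that named one decisive model would have to depart from a published sentence that names four.

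**Conclusion.** The point holds as a defect of specification. The article gives four methods primary status, names none as decisive for the medicine proportions, and leaves them unreconciled with its own two-level approach and with the abstract. The choice between them could therefore be made after the results are seen.

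The size is conditional on two-sided 5% per test and on any significant primary test being reportable. For one medicine and one arm contrast it is about 5% when the tests share a physician-level summary, and roughly 9-11% when a follow-up comparison, the arm-by-time ANOVA and a baseline-adjusted regression are all open. The full range is about 5% to 18%, depending on the correlation between tests. It should not be reported as an error rate that the trial has. Multiplicity from several medicines, arms and time points is a separate matter and is not counted here.

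**What to change.** Replace the sentence on methods with one that names a single decisive analysis for each primary outcome: a two-level logistic regression of prescriptions within randomised physicians, allowing for variation between physicians and reported as the arm-versus-arm contrasts in the objectives. State that this model alone decides each primary outcome. Confine chi-square and t-tests to descriptive baseline tables, and label the repeated-measures ANOVA a sensitivity analysis that cannot overturn the primary result. Align the abstract's reference to regression with this model.

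The cost is a small text change, with no new data or participants. The one thing given up is the freedom to present another test as primary.

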### Sample size calculation and allocation to the intervention arms

Considering that about 14% of outpatient prescriptions in Tehran contain dexamethasone injections and expecting that the intervention may reduce such prescriptions by 10%, we aimed to recruit 200 participants in each study arm (i.e. a total 800 participants).

As the interventions will be delivered to all the physicians allocated to the study arms (effectiveness trial) and that we used routinely collected data to assess the effects, the prospect of loss to follow was low.

To allocate the participants to the study arms, we first prepare a list of all eligible physicians working in Tehran (about 6000 physicians). The physicians will be grouped into the three physician groups (i.e. general physicians, pediatricians, infectious disease specialists). Within each group we will randomly select the required number of physicians, proportional to the size of each group. Using a random number generator, the participants will be allocated to the study arms, and use the physician group and the contracted insurance organization as the stratifying factors. As a result we will have, in each study arm, 175 general physicians, 24 pediatricians, and four infectious disease specialists (totaling 203 physicians in each arm). Random numbers will be generated by a member of the team who is not involved in the delivery of the interventions.

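### The named primary methods are not tied to baseline or stratification covariates, and repeated-measures ANOVA over the collected times would count baseline as an outcome

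*Protocol article*

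**What the plan says.** Under Statistical and cost-effectiveness analyses, the protocol names chi-square and t-test and continues that "repeated measure ANOVA and logistic regression analyses will be the primary modes of analyzing the results". The same section adds a multilevel statement ("A fixed-effect two-level analysis approach will be followed in which prescriptions will be used as the first level", with physicians as the second level) and a general one on interactions ("Appropriate interaction analyses will be conducted to assess the interactions between the selected variables and the interventions"). It names no covariate, and does not say which time points enter the repeated-measures analysis or which of its terms is the test of the intervention.

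Three other statements bear on this:

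- **Allocation** (Sample size calculation and allocation to the intervention arms): the trialists will "use the physician group and the contracted insurance organization as the stratifying factors".
- **Timing** (Study procedures and data collection): "Data at baseline, one month and 3 months after the intervention will be collected".
- **Outcome.** Outcome measures defines it as "the percentage of change in the proportion of dexamethasone injectable form, oral form of cefixime and amoxicillin", which is a change from baseline. The analysis section says instead that "we will assess the effects of the study arms on the proportion of prescriptions containing each of the target prescribed medicines", with no mention of change.

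The one use that the analysis section itself gives to baseline data is a comparability check: "Demographic and baseline analyses will be conducted to ensure random allocation procedure has been effective in producing comparable study arms".

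**The concern.** Each physician's own past prescribing is likely to predict later prescribing strongly, and here it comes from claims data at no extra cost. The two stratification factors are also known for everyone. A primary analysis that ignores them gives away precision. After stratified allocation, an unadjusted comparison also tends to overstate its standard error.

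Repeated-measures ANOVA raises a further question. One of the three collected times precedes the intervention, when no arm can differ except by chance. If that time is a level of the response and the arm main effect is tested, a null period is averaged into the effect.

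The two descriptions of the outcome leave the role of baseline open. One builds it into the outcome as a change; the other does not mention it. Several primary modes are listed, so the analyst could choose among tests of very different efficiency.

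**Working it through.** **The plan's own figure.** The protocol gives 200 physicians per arm from a 14% dexamethasone rate and a 10% reduction. Alpha, power, SD, ICC and baseline correlation are not stated, so 200 cannot be reproduced. Treating units as independent, two-sided 5%, a relative reading (14% to 12.6%) needs 9,235 per arm for 80% power. An absolute reading (14% to 4%) needs 128 per arm for 80%, 171 for 90% and 210 for 95%. The figure therefore fixes no target against which to measure a loss.

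**Dilution.** With effect 0 at baseline and d at months 1 and 3, the arm main effect estimates (0 + d + d)/3 = 2d/3. For d = 1.4 points (the relative reading) that is 0.93 points.

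**Relative efficiency.** Assume three equally correlated times (correlation ρ), equal variance and constant d. The variance of the estimated effect, rescaled to estimate d and in units of one unadjusted follow-up comparison, is:

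- one follow-up, unadjusted: 1
- mean of the two follow-ups, unadjusted: (1 + ρ)/2
- arm main effect over all three times: [(1 + 2ρ)/3] / (2/3)² = 0.75 + 1.5ρ
- change of the follow-up mean from baseline: 1.5(1 − ρ)
- ANCOVA of the follow-up mean on baseline, call it A: (1 + ρ)/2 − ρ²

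Subtracting A gives an ordering that needs no value of ρ:

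- unadjusted follow-up mean − A = ρ² ≥ 0
- change − A = (1 − ρ)² ≥ 0
- arm main effect − A = (0.5 + ρ)² ≥ 0

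Sample size relative to ANCOVA (ρ is not in the protocol and is assumed):

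| ρ | Arm main effect | Change | Follow-up mean, unadjusted |
|---|---|---|---|
| 0.3 | 2.14 | 1.87 | 1.16 |
| 0.5 | 3.00 | 1.50 | 1.50 |
| 0.7 | 5.00 | 1.25 | 2.36 |
| 0.9 | 15.0 | 1.07 | 6.79 |

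For two arms, the arm-by-time test has the change contrast's noncentrality spread over 2 df, so it lies below the change contrast. For all four arms it has (4 − 1)(3 − 1) = 6 df.

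**Illustrative power.** From the protocol: 14%, 203 per arm, and d = 1.4 points on the relative reading. Assumed: 100 prescriptions per physician and period, physician-level correlation between periods 0.8, two-sided 5%, pairwise comparison, normal approximation.

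- Variance per physician: σ² = 0.14 × 0.86 × [ICC + (1 − ICC)/100]
- Correlation of observed proportions: ρ = 0.8 × ICC / [ICC + (1 − ICC)/100]
- z for one follow-up: 0.014 / (σ√(2/203)), divided by the square root of the factor above for each other test

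At ICC 0.05: σ = 0.0846, ρ = 0.672 and z = 1.666. The ANCOVA factor is 0.384, so z = 1.666/√0.384 = 2.69 and power = Φ(2.69 − 1.96) = 76.7%.

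| Test | ICC 0.05 | ICC 0.10 | ICC 0.20 |
|---|---|---|---|
| Arm main effect, baseline included | 24.2% | 14.8% | 9.9% |
| Month 3, unadjusted t-test | 38.5% | 23.4% | 14.5% |
| Mean of months 1 and 3, unadjusted | 44.5% | 26.2% | 15.8% |
| Arm-by-time, 2 df | 55.7% | 39.7% | 25.4% |
| Change, mean of months 1 and 3 | 66.2% | 49.6% | 32.8% |
| ANCOVA, mean of months 1 and 3 | 76.7% | 57.5% | 37.7% |

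The change row approximates the plan's percentage change by an absolute change. ANCOVA's advantage is 4.9 to 10.5 points over change, 12.3 to 21.0 over arm-by-time, 21.9 to 32.2 over the unadjusted follow-up mean, 23.2 to 38.2 over the month-3 t-test, and 27.8 to 52.5 over the arm main effect.

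**Strata.** If physician group and insurer explain a further share R² of the variance, the standard error falls by 1 − √(1 − R²): 5.1% at R² = 0.10 and 10.6% at 0.20. Both R² values are assumptions.

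**Absolute reading.** An effect of 10 points multiplies each z by 10/1.4 = 7.14. The weakest cell (arm main effect, ICC 0.20, z = 0.646) becomes 4.61, with power above 99%. On that reading the cost is precision, not power.

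**The case against.** A reader might infer that the plan leaves baseline and the strata out of the primary analysis and so shrinks the effect by a third. The protocol does not support that.

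- **Silence is not exclusion.** No covariate is named, but none is ruled out. Logistic regression and the two-level model can both carry covariates, the abstract speaks of regression analyses, and a covariate list is often left to a statistical analysis plan, which is not shown here.
- **Baseline is used elsewhere.** The percentage-change outcome uses each physician's own baseline, so it is wrong to say that baseline is discarded.
- **The dilution is conditional.** It needs baseline as a response level and the arm main effect as the test. The protocol fixes neither, and the arm-by-time term carries the full effect.
- **Fixed effects may absorb baseline.** If the two-level approach means physician fixed effects across periods, stable differences between physicians drop out.
- **No baseline significance tests are written.** The comparability check may be purely descriptive.
- **The power figures rest on assumptions.** The 100 prescriptions a month in the protocol is an eligibility minimum, not an analysed count.

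All of this stands and limits the claim. What remains is that the protocol does name its primary modes. Two of the four cannot adjust, and a third, applied to the times collected, makes baseline a response. Change scores and, in a linear model, physician fixed effects avoid the dilution, but the algebra above shows that they never beat adjustment on the same follow-up data.

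**Conclusion.** The point holds as a badly fixed choice of primary method, not as a demonstrated error or bias. Unadjusted comparisons after stratified randomisation remain valid, if conservative. The loss is in efficiency and in having no single stated primary model.

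The ordering of methods follows from algebra under equal correlation and a constant effect. Its size does not follow from the protocol: it depends on ICC, period correlation, prescriptions per physician and the reading of the 10% reduction. On the relative reading with the assumed values, the gain is modest against a change score (about 5 to 11 points) and larger against unadjusted tests (about 22 to 38). The figures for the diluted main effect apply only if that term is the test, which the protocol does not say.

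This is a free improvement and worth making.

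**What to change.** Name one primary model for each target medicine, with clustering by physician:

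- outcomes: months 1 and 3 only;
- terms: arm, the physician's baseline proportion of the same medicine, physician group and contracted insurer;
- strata as main effects only, because each arm has just four infectious disease specialists;
- the arm contrast that answers each stated objective.

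Reconcile Outcome measures (percentage change) with the analysis section (proportion), so that baseline enters once, as a covariate. Keep chi-square and t-test as descriptive or sensitivity analyses, and do not use repeated-measures ANOVA with baseline as a response level for the primary test. Present baseline characteristics by arm descriptively.

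The cost is a few sentences. The strata are known from allocation and the baseline comes from claims data already planned, so no new data or participants are needed.

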### Study setting and participants

The study is conducted in Tehran. All general physicians, pediatricians and infectious disease specialists who have an outpatient practice in Tehran, issue a minimum of 100 prescriptions per month, and have a current contract with at least one of the two main social health insurance organizations are eligible for inclusion in the study.

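### Physicians are randomised, but the plan specifies a fixed-effect physician level and gives no unit of analysis for its primary tests, so it does not secure a valid standard error for the arm effect

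*Protocol article*

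**What the plan says.** The unit of randomisation is the physician. The abstract states that "Physicians working in outpatient practices are randomly allocated to one of the four arms using stratified randomized sampling", and the section on sample size and allocation says that "the participants will be allocated to the study arms, and use the physician group and the contracted insurance organization as the stratifying factors", "totaling 203 physicians in each arm". Under Study setting and participants, an eligible physician must "issue a minimum of 100 prescriptions per month".

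The section on statistical and cost-effectiveness analyses makes three statements about method:

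- After naming chi-square and t-test, it says "repeated measure ANOVA and logistic regression analyses will be the primary modes of analyzing the results". No unit of analysis is given for any of the four.
- "A fixed-effect two-level analysis approach will be followed in which prescriptions will be used as the first level and the physicians as the second level". No random physician effect, cluster-robust standard error or intracluster correlation (ICC) is mentioned.
- "Intention-to-treat analyses will be carried out with physicians as the primary analysis approach".

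The primary outcome in that section is the proportion of prescriptions that contain each target medicine. The Outcome measures section words it as a percentage change in that proportion. Data are collected at baseline, one month and three months.

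**The concern.** Prescriptions by one physician resemble each other, and every one of them belongs to the same arm. The precision of an arm comparison is therefore limited by how much physicians differ, not by the number of prescriptions alone. The only description given of the two-level model is that it is fixed-effect. Taken literally, that means one parameter per physician. Arm never varies within a physician, so those parameters absorb it. Bringing in baseline data makes an arm-by-period contrast available, but a fixed physician level treats every physician as having the same change apart from binomial noise.

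The four named tests do not settle the matter, because nothing ties each to prescriptions or to physician summaries. An analyst who follows the text could pick a procedure that holds its 5% level or one that exceeds it several-fold. The authors hope that successful formats will be applied nationwide, so a false-positive result would have practical consequences.

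**Working it through.** **Inputs from the article.** 203 physicians per arm; at least 100 prescriptions per physician per month, so m = 100 as the minimum for one month; and a baseline rate of 14% ("about 14% of outpatient prescriptions in Tehran contain dexamethasone injections").

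**Assumptions.** ICC from 0.01 to 0.20, and between-period correlation r of a physician's true rate from 0.5 to 0.95. The article gives neither. The checks use one two-arm comparison, nominal two-sided 5%.

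**The plan's own figures.** The article states no standard error, ICC or type I error to reproduce. Its 200 physicians per arm is not in dispute here and cannot be confirmed, because alpha, power and the meaning of the 10% reduction are not stated.

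**Step 1: can the arm effect be estimated?** In a 40-physician example, the physician indicators have rank 40, and adding arm leaves the rank at 40. The arm main effect is therefore not estimable. With baseline and follow-up periods, the design with physician, time and arm-by-time terms has rank 48 for 48 columns. The arm-by-period effect is estimable.

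**Step 2: the arm-by-period contrast with fixed physician effects.** The model uses prescription-level residual variance only. The true variance exceeds it by a factor of approximately

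V = 1 + m × ICC × (1 − r) / (1 − ICC),

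and the type I error is approximately 2 × [1 − Φ(1.96/√V)].

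- ICC 0.01, r 0.95: V = 1 + 100 × 0.01 × 0.05/0.99 = 1.05, giving 5.6%.
- ICC 0.05, r 0.8: V = 1 + 100 × 0.05 × 0.2/0.95 = 2.05, giving 17.1%.
- ICC 0.10, r 0.5: V = 1 + 100 × 0.10 × 0.5/0.90 = 6.56, giving 44.4%.

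Simulation under the null (3,000 runs per setting) agrees:

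| ICC | r = 0.95 | r = 0.8 | r = 0.5 |
|---|---|---|---|
| 0.01 | 5.4% | 7.5% | 11.6% |
| 0.05 | 7.2% | 17.6% | 30.3% |
| 0.10 | 10.9% | 28.8% | 45.2% |

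**Step 3: tests on pooled prescriptions, if that is what is meant.** The design effect is DE = 1 + (m − 1) × ICC. The standard error is too small by a factor √DE, and the type I error is 2 × [1 − Φ(1.96/√DE)]. The naive standard error is √(2 × 0.14 × 0.86/20,300) = 0.0034, with 203 × 100 = 20,300 prescriptions per arm.

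| ICC | DE | √DE | Type I error |
|---|---|---|---|
| 0.01 | 1.99 | 1.41 | 16.5% |
| 0.02 | 2.98 | 1.73 | 25.6% |
| 0.05 | 5.95 | 2.44 | 42.2% |
| 0.10 | 10.9 | 3.30 | 55.3% |
| 0.20 | 20.8 | 4.56 | 66.7% |

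With m = 300 and ICC 0.05, DE = 15.95 and the type I error is 62%, so busier physicians or a longer window make it worse.

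**Step 4: physician-level summaries.** A t-test on each physician's follow-up proportion, or on the change from baseline, gave a simulated type I error between 4.1% and 5.8% over ICC 0.01 to 0.10 and all three values of r.

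**The case against.** A reader might infer that the plan's primary tests are run on pooled prescriptions and that the 17% to 67% error rates are therefore the plan's own. The article does not support that. It never states the level at which the four tests are run. Repeated-measures ANOVA over three time points fits physician summaries, since only the physician is measured repeatedly, and so does a t-test on proportions or change. The intention-to-treat sentence refers to physicians. That part of the objection stands. It covers chi-square and ordinary logistic regression less well: both need a categorical outcome, and the natural one is whether a prescription contains the medicine.

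A reader might also infer that the arm effect must be either not estimable or have a standard error far too small. Nor does that follow. Baseline data are collected and the outcome is worded as change, so the arm-by-period contrast is available, and Step 2 shows it close to nominal when the ICC is low and physician rates are stable.

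Finally, fixed-effect may be loose wording for fixed arm effects with a random physician intercept, and the two-level sentence does recognise the clustering. That reading is possible and would be valid for a follow-up comparison. It is not a full rescue once baseline is modelled: in a balanced linear model a random intercept alone gives the same arm-by-period estimate and standard error as physician indicators, so the inflation in Step 2 returns.

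A condensed article may leave much to a fuller plan. Here, however, the article states a rule for the physician level, and that rule read as written can give a wrong result.

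**Conclusion.** The concern holds, with consequences that depend on how the text is read. As written, the physician level is specified as fixed-effect although physicians are the randomised unit, and the named primary tests have no stated unit.

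Under the literal reading, a post-intervention arm effect cannot be estimated, and the arm-by-period test has a type I error of about 5% to 45% over the assumed range (ICC 0.01 to 0.10, correlation 0.95 to 0.5). If chi-square or plain logistic regression is applied to pooled prescriptions, it is about 17% to 67% (ICC 0.01 to 0.20). If physician summaries are used, it is about 5%. These figures rest on 100 prescriptions per physician and period, equal for all physicians, and on an ICC and a between-period correlation that the article does not give. Nothing in the article shows which part of the range applies.

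**What to change.** Name one primary analysis that respects clustering by physician, chosen in advance from:

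- a mixed logistic model on prescriptions with a random physician intercept, plus a random physician-by-period effect when baseline prescriptions are modelled;
- GEE with physicians as clusters and robust standard errors;
- physician-level ANCOVA of the follow-up proportion on the baseline proportion.

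These are not interchangeable. The ANCOVA estimates a difference in mean proportions and the mixed model a conditional odds ratio, so the choice also fixes the estimand.

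Remove the fixed-effect label from the physician level. State that any chi-square, t-test, ANOVA or logistic regression used for arm effects is based on physician summaries or cluster-adjusted standard errors.

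This is a change of wording in the analysis section and needs no further data. The cost is wider confidence intervals than the literal fixed-effect model or a pooled prescription-level test would report.
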